## Study intervention

### ACT-DNA-v

Uses language, metaphors, mindfulness and experiential learning to encourage young people to defuse distressing psychological experiences and adopt an accepting stance towards one's experience as it unfolds in real-time while pursuing behavioral goals derived from personal life value. This enables them to engage in value-led behaviors such as medication adherence.

The intervention involves four sessions delivered in six weeks, with each session lasting two hours a week, for a total of 12 hours. The sessions will be delivered by HCPs (counsellors) together with the research team. All four sessions strengthen the appropriate use of discover, noticer and advisor skills in line with values to improve psychological flexibility.

Table 1; showing sessions of the ACT-DNA-v

|           |                                                                                                |
|-----------|------------------------------------------------------------------------------------------------|
| Session 1 | About DNA-V, being yourself, using social DNA to build groups, the challenge of choosing       |
| Session 2 | The Noticer: normalizing noticer, practice awareness, noticer sessions, responding to signals  |
| Session 3 | The Advisor: normalizing adviser, helpfulness of advisor, games to unhook from advisor         |
| Session 4 | Discoverer: meeting your discoverer, build strength, try it-track it-build it, DNA-V in action |
| Session 5 | Values: small things matter, introduction of values, value is success                          |
| Session 6 | Who you are, making yourself, ways of well-being, social DNA, and closure.                     |

#### Outcome measures.

Measured clinical primary outcomes will include Experiences of depression, anxiety and internalized stigma. Then process outcomes will include; Psychological flexibility (cognitive fusion and experiential avoidance) to test the mechanism of change and secondary outcomes will be; self-reported adherence and viral load (obtained from clinical charts).

Table 2; Showing study measures, analysis and outcomes.

| Objective                                                             | Variables                                                                                                                                      | Informant | Measures                                                                                                                                                                                                                                                                                                                                                                                                                                                      | Analysis & Outcomes                                                                                                                                                                                                                                                                                                                                                                             |
|-----------------------------------------------------------------------|------------------------------------------------------------------------------------------------------------------------------------------------|-----------|---------------------------------------------------------------------------------------------------------------------------------------------------------------------------------------------------------------------------------------------------------------------------------------------------------------------------------------------------------------------------------------------------------------------------------------------------------------|-------------------------------------------------------------------------------------------------------------------------------------------------------------------------------------------------------------------------------------------------------------------------------------------------------------------------------------------------------------------------------------------------|
| To adapt and measure the feasibility of ACT-DNA-v for use with ALWHA. | *Enrollment
*Attendance
*Retention in the study.
*Completion of sessions and assignments.
*Assessments completed and missing data. | ALWHA     | *Number of ALWHA's referred, the percentage who are eligible and the number consented.
*Number of sessions attended and reasons for non-attendance.
*Number of participants who stay in the study till the end (screening baseline, intervention & follow-up) and reasons for withdrawal.
*Number of participants completing all assessments (including participant feedback regarding acceptability of data collection methods, duration& content). | *Analysis; Descriptive statistics; summarizing recruitment, demographics, attendance, attrition and intervention adherence.
*Outcomes will include; % of participants consented out of those contacted, % of participants retained, % of participants completing all sessions, % of participants completing assignments, % of participants dropping out of study and reasons for withdrawal. |

|                                                                                                                                                    |                                                         |       |                                                                                                                                                                                                                                                |                                                                                                                                                                                                                                                                                                                                                                                                                                                                                                                                                                                                                                                                                                                                                                                                                                           |
|----------------------------------------------------------------------------------------------------------------------------------------------------|---------------------------------------------------------|-------|------------------------------------------------------------------------------------------------------------------------------------------------------------------------------------------------------------------------------------------------|-------------------------------------------------------------------------------------------------------------------------------------------------------------------------------------------------------------------------------------------------------------------------------------------------------------------------------------------------------------------------------------------------------------------------------------------------------------------------------------------------------------------------------------------------------------------------------------------------------------------------------------------------------------------------------------------------------------------------------------------------------------------------------------------------------------------------------------------|
| To examine the impact of ACT-DNA-v on reducing proximal psychosocial barriers to medication adherence (depression, anxiety and stigma) among ALWHA | Depression
Anxiety
Internalized stigma            | ALWHA | Qualitative surveys using standardized data collection instruments.
* Reynolds Adolescents depression scale (RADS-2)
* Social anxiety scale for adolescents-short form (SA-A-SF).
* Internalized AIDS-related stigma scale (IARSS-6). | 
Analysis
We shall run a T-test, linear regression, and Fisher's exact and Chi-square tests respectively to obtain mean differences between groups.
 
Outcomes we hypothesize that;
*The average means score of ALWHA in the intervention arm should be in the mild depression range of the BDI-ii (14-19) at post-intervention and follow-up, adjusting for baseline compared to the mean score of ALWHA in the control group.
* The average mean score of ALWHA in the intervention arm should be below the cutoff score of 40.5 as measured by the SHAI at post-intervention and follow-up.
* After dichotomizing the IARSS-6 at median value (0-2 & 3-6), average mean scores of participants in the intervention arm should fall in category1 (0-2) at post-intervention and follow-up.
 |
| To measure the effectiveness of a mindfulness-based intervention (ACT-DNA-v) on psychological flexibility among ALWHA in Kampala.                  | Process variable:
*Psychological flexibility. | ALWHA | Qualitative surveys using standardized self-administered instruments

* Avoidance and Fusion Questionnaire for youths (AFQ-Y8).                                                                                                          | 
Analysis
We shall run a T-test, linear regression, and Fisher's exact and Chi-square tests respectively to obtain mean differences between groups.
 
Outcomes
*The average mean scores of participants in the intervention group will be above the cut-off score on psychological inflexibility using the AFQ-8 at post-intervention and follow-up adjusting for baseline scores.
                                                                                                                                                                                                                                                                                                                                                                                                                       |

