### Methods

Sequential multi-methods design will be used, commencing with a formative phase where ACT-DNA-v will be adapted to fit the specific needs of users and providers in Kampala and using semi-structured interviews, explore the acceptability of ACT-DNA-v among users and providers, as well as implementation related factors. This phase will be followed by measuring the feasibility and effectiveness of the adapted ACT-DNA-v in improving mental health outcomes among ALWHA with a randomized control trial (RCT). The trial will involve quantitative surveys at baseline, post-intervention and follow-up, testing the effects of the intervention on process and clinical outcomes among ALWHA. Thematic analysis that involves coding, analysis and interpretation of findings utilizing qualitative data analysis software (QDA) will be used for the qualitative study, while T-test, Fisher's exact, regression, Chi-square tests and analysis of variance (ANOVA) respectively will be used in the quantitative phase to ascertain average mean differences between the two study groups on the outcome parameters of depression symptoms, anxiety, and stigma at pre-post intervention and psychological flexibility at follow-up.

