### Hypothesis.

- (i) Participants receiving the ACT-DNA-v intervention will report a significant reduction in depression, anxiety & stigma at post-intervention assessment as compared to participants in the control group.

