##### *Inclusion Criteria:*

Participant should be 15-19 years of age, diagnosed HIV positive, attending care at Kisenyi Kitebi health center for the last 6 months, on first or second line of treatment, can speak/understand

Luganda or English and willing to provide informed consent/assent. All records will be confirmed via clinic medical charts.

*Exclusion criteria:*

A participant will not be eligible to be part of the study if he/she plans to move out of the catchment area within six months, or if he/she is participating in another study related to HIV and care improvement.

*Sampling for sub-study two*

*Sample size*

The following assumptions are considered for determining the appropriate sample size for the quantitative study.

Assumptions:

$$N = 2 \frac{[Z\alpha + Z\beta]^2 S^2}{(\mu_1 - \mu_2)^2}$$

where:

$Z\alpha$  is standard normal value corresponding to level of significance

$Z\beta$  is standard normal value corresponding to power of the study

$\alpha$ =acceptable type 1 error

$\beta$ = type II error

$\mu_1$  is mean in control group and  $\mu_2$  is mean intervention

$\mu_1 - \mu_2$  =effect size (minimum meaningful difference between the means in the control and intervention groups)

$S$ =standard deviation of the outcome in the control group

$N$  is the sample size per group

$Z\alpha = 1.96$ ,  $Z\beta = 0.84$ ,  $\alpha = 0.05$  in 2 tails,  $\beta = 0.20$  (at 80% power).

Considering a study evaluating effectiveness of Acceptance and Commitment Therapy (ACT) on reducing the depressive symptomatology among Swedish and Australian adolescents (Livheim et.al, 2015), the difference in means of the post treatment RADS2 scores between the ACT arm and control arm was 4.09 while the standard deviation in the control arm was 5.13.

Substituting into the formula,

$$N = (2(1.96 + 0.84)^2 \times 5.13^2) / (4.09^2)$$

$$N = 25.1$$

N=26 participants in each group

If we consider a possible clustering in any of the two sites and a design effect of 2.0, the new minimum sample size is  $26 \times (2) = 52$ . If we consider a 10% loss to follow-up, the revised sample size will become  $(52 \times (1 / (1 - 0.10))) = 58$  participants. We, therefore, aim to recruit, **a total of 116 participants** at 80% power of detecting a mean difference of 4.09 or more in the intervention.

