#### Data collection and measures

For feasibility assessment: observation, checklists and survey will be used to collect data. The feasibility measures will include; i) enrollment (number of ALWHA's referred, proportion of those who are eligible and the number that consent), ii) attendance (number of sessions attended and completed and reasons for non-attendance iii) Retention in the study (number of participants completing all sessions and assignments) iv) number of assessments completed and missing data and v) self-rated program acceptability (helpful, meaningful, relevant and interesting).

When evaluating the effectiveness of a mindfulness and acceptance-based intervention, standardized survey instruments and document review will be used to collect data at baseline and post-intervention respectively.

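### Three unranked primary outcomes have no any-or-all success rule and no error control between them, the sample size covers depression alone, and the time point of the primary comparison conflicts.

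*Protocol*

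**What the plan says.** **Outcomes.** The Outcome measures section reads: "Measured clinical primary outcomes will include Experiences of depression, anxiety and internalized stigma". It gives no order, time point or success rule.

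**Claim.** Under Hypothesis, participants in the intervention arm "will report a significant reduction in depression, anxiety & stigma at post-intervention assessment" compared with control. The joining of the three outcomes can be read as all of them or as each of them.

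**Time point.**
- The Abstract (Methods) compares the arms on "depression symptoms, anxiety, and stigma at pre-post intervention and psychological flexibility at follow-up", so follow-up is attached to the process measure only.
- Data collection and measures says the effectiveness instruments "will be used to collect data at baseline and post-intervention respectively".
- Table 2 sets targets at both times for each clinical outcome. For anxiety, the intervention-arm mean "should be below the cutoff score of 40.5 as measured by the SHAI at post-intervention and follow-up".
- The Schedule of activities includes a follow-up assessment but does not call it primary.

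**Tests.** Table 2 says: "We shall run a T-test, linear regression, and Fisher's exact and Chi-square tests respectively to obtain mean differences between groups". It gives no order and no rule across outcomes. The only multiplicity rule, in the Data Safety and Monitoring Committee section, is a Bonferroni adjustment for interim analyses.

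**Sample size.** The calculation uses a RADS-2 difference of 4.09 and a standard deviation of 5.13 from a cited study of ACT in adolescents. It ends with 116 participants "at 80% power of detecting a mean difference of 4.09 or more in the intervention". Anxiety and stigma have no effect size, standard deviation or power.

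**The concern.** With three co-listed primary outcomes, the trial's error rate and power depend on what counts as success, and the protocol does not say. If a significant result on any one outcome is enough, testing each at 0.05 raises the chance of a false claim above 5%. If all three must be significant, the error rate is controlled but the power is lower than for depression alone.

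At stake is how the result is read. A significant difference on stigma alone could be reported as success on a primary outcome. A real depression effect could be called a failure because stigma did not change. The uncertain status of follow-up adds a second choice that could be made after the data are seen.

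**Working it through.** **Inputs from the protocol.** Two-sided alpha 0.05, power 80%, difference 4.09, SD 5.13, design effect 2.0, loss to follow-up 10%, 1:1 allocation (Sample size; Randomization). The standardized effect is d = 4.09/5.13 = 0.797.

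**Assumptions.** The protocol gives no correlations between outcomes or between times, so 0 to 0.7 is used. It gives no effect for anxiety or stigma, so the depression effect is used for all three unless stated.

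**1. The protocol's own figure.** n = 2 × (1.96 + 0.84)² × 5.13² / 4.09² = 24.67, so 25 per arm. The protocol has 25.1, so 26. From 26: 26 × 2 = 52; 52/0.90 = 57.8, so 58 per arm and 116 in total, as stated. Starting from 25 the total would be 112, a small difference that does not affect this point.

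**2. False-positive rate if any one outcome counts (no true effect on any of them).**
- Three independent tests: 1 − 0.95³ = 14.3%.
- Three correlated tests, simulated with 1,000,000 draws: 12.5% at correlation 0.5 and 10.9% at 0.7.
- Six independent tests (three outcomes at two times): 1 − 0.95⁶ = 26.5%.
- Six tests with outcomes and times both correlated: 21.9% at 0.5 and 17.6% at 0.7.

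**3. Power if all three must be significant.** The protocol expects 52 evaluable per arm. With its design effect of 2, these are worth 52/2 = 26. For one outcome, power = Φ(d√(n/2) − 1.96).
- n = 26: Φ(2.87 − 1.96) = 82.0%.
- n = 52 (no design effect): Φ(4.07 − 1.96) = 98.2%.

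| Requirement | Effective 26 per arm | 52 per arm, no design effect |
|---|---|---|
| One outcome, alpha 0.05 | 82.0% | 98.2% |
| All three, independent (cube of the line above) | 55.1% | 94.8% |
| All three, correlation 0.7 (simulated) | 68.7% | 96.1% |

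**4. If anxiety or stigma has a smaller effect.** With an assumed d of 0.5, power for one such outcome at 0.05 is 44% (effective 26) to 72% (52 per arm).

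**5. What adjustment would cost under the protocol's design effect.**
- Bonferroni over three tests (alpha 0.0167): power for one outcome at the effective 26 is 68.5%. Restoring 80% needs 33 per arm; 33 × 2 = 66; 66/0.90 = 73.3, so 74 per arm and 148 in total.
- Bonferroni over six tests (alpha 0.0083): power is 59.3%. Restoring 80% needs 39 per arm; 39 × 2 = 78; 78/0.90 = 86.7, so 87 per arm and 174 in total.
- All three required, 80% power: 33 (correlation 0.7) to 37 (independent) per arm before inflation, giving 148 to 166 in total.
- One primary outcome at one time: 116 stands, provided its inputs hold for the chosen instrument.

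**The case against.** The strongest reply is that the division of alpha is commonly left to a statistical analysis plan, which is not shown here, and that the Hypothesis can be read as one joint claim needing no adjustment. The protocol also describes its aim as preliminary effectiveness (Purpose Statement; Sub-study Two), which asks less of a formal hierarchy.

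Much of this stands. The adjustment method can be set elsewhere, and the stated aim lowers the severity. But the analysis plan would inherit three unranked primary outcomes, a sample size for one of them and conflicting time points. Adding an adjustment later would also change the power (step 5). The protocol still states a significance hypothesis, a formal power calculation and a stopping rule based on a very small P value.

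Three stronger readings are tempting but not supported:
- *Six declared primary tests.* Only Table 2 brings follow-up into the clinical outcomes. Its entries are target levels, and those for anxiety and stigma describe the intervention arm's mean without a control comparison. The tests are listed without a time point. Six is an upper count under one reading, and 26.5% also needs independence. That is implausible for repeated measurements, and the protocol itself reports that the stigma scale correlates with depression.
- *Power is certainly below 80%.* The shortfall depends on the design effect, which the protocol adds for possible clustering. Without it, power for all three is about 95% if they share the depression effect.
- *No claim can be confirmed.* There is one stated hypothesis; what is missing is its success rule.

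**Conclusion.** The point holds in this form: three unranked primary outcomes, no any-or-all rule, no error control between them in the protocol, a sample size for depression alone, and passages that disagree on the time point.

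Under an any-of-three rule at two-sided 0.05, the false-positive rate is about 11% to 14%, or about 18% to 26% if follow-up is counted too. Under an all-of-three rule, power is about 55% to 69% with the protocol's design effect and about 95% without it. These ranges rest on assumed correlations of 0 to 0.7, and the power figures also on a common effect that the protocol does not claim for anxiety or stigma.

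This should be corrected before arms are compared. Given the preliminary aim, it does not undermine the trial as a whole.

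**What to change.** - Name depression at post-intervention as the single primary outcome, on one stated instrument. First reconcile RADS-2 (Sample size; Table 2 measures column) with BDI-II (Study instruments; Table 2 target), then recheck the difference and standard deviation for the chosen scale. Without this step the primary outcome would remain undefined.
- Make anxiety and stigma at post-intervention key secondary outcomes, tested with Holm adjustment only if depression is significant.
- Make all follow-up comparisons secondary.
- Align the Abstract, Hypothesis, Data collection and measures, Outcome measures and Table 2.

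If the sponsor prefers to keep all three as primary, state whether success means any or all, apply Holm for any, and restate the power for that rule with stated effects for anxiety and stigma.

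**Cost.** The preferred route needs wording changes and the recheck of inputs; the total stays at 116 if those inputs hold. Anxiety and stigma lose primary status, although the objectives and publication plan treat the three alike. The alternative keeps their status but makes the stated power less favourable, or requires a larger sample of the order shown in step 5.

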## List of abbreviations

**ACT:** Acceptance and Commitment Therapy

**AFQ-Y:** Avoidance and Fusion Questionnaire for youth

**AIDS:** Acquired Immunodeficiency Syndrome.

**ALWHA:** Adolescents Living with HIV/AIDS

**ANCOVA:** Analysis of Covariance

**ART:** Antiretroviral Therapy.

**CBTs:** Cognitive Behavioral Therapies

**DNA-v:** Discoverer, Noticer and Advisor-values model

**FGDs:** Focus Group Interviews

**HBM:** Health Belief Model

**HCPs:** Health Care Providers (Counselors)

**HIV:** Human Immunodeficiency Virus.

**IARSS:** Internalized AIDS-Related Stigma Scale

**IDI:** In-Depth Interviews

**KCCA:** Kampala Capital City Authority

**KHCIV:** Kisenyi Health Center IV

**KTHCIII:** Kitebi Health Center iii

**RFT:** Relational Frame Theory

**SAS-A-SF:** Social anxiety scale for adolescents, short version.

**SOM-REC:** School of Medicine Research and Ethics Committee.

**SSA:** Sub-Saharan Africa

**UNCST:** Uganda National Council for Science and Technology.

**VLS:** Viral Load Suppression

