#### *Randomization*

Participants will be randomly allocated to the intervention or control group using computer-generated random numbers. A block size of six with equal individuals going to the two arms per block will be considered sufficient to obtain individuals allocated in a ratio of 1:1 in terms of intervention to the control groups.

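### Table 2 assigns Fisher's exact and chi-square tests to mean differences they cannot give, and states baseline adjustment for depression and psychological flexibility but not for anxiety or stigma

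*Protocol*

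**What the plan says.** The analysis of the outcomes is set out in Table 2 of the protocol, under Outcome measures. The row for depression, anxiety and stigma and the row for psychological flexibility carry the same line: a t-test, linear regression, and Fisher's "exact and Chi-square tests respectively to obtain mean differences between groups".

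In the hypothesised results beside that line, depression on the BDI-II is to be judged "adjusting for baseline compared to the mean score of ALWHA in the control group", and the AFQ-Y8 entry also mentions adjustment for baseline scores. The SHAI and IARSS-6 entries mention none. The IARSS-6 is also to be split into 0-2 and 3-6.

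The Sub-study design section collects depression, anxiety, stigma and psychological flexibility at baseline. The Statistical analysis section gives the same list of tests for the table of baseline characteristics, there linked to continuous and categorical variables, and sends the outcome comparisons back to Table 2. The Methods paragraph of the abstract adds "analysis of variance (ANOVA) respectively will be used in the quantitative phase". The term "Analysis of Covariance" appears only in the List of abbreviations.

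**The concern.** Two things in Table 2 are fixed badly.

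First, the tests do not match the quantity. Chi-square and Fisher's exact tests compare proportions and yield no mean difference. A t-test cannot carry a baseline score, whereas a linear regression can, and the table names both without saying which one the conclusion rests on.

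Second, the adjustment is uneven. Two scales are described as baseline-adjusted and two are not, with no reason given, although the baseline score of each is available. The two left out are clinical primary outcomes.

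At stake are precision and a clear rule. Without the baseline score, the variation between adolescents that was already present before treatment stays in the error term. Without a governing method, the reader cannot tell which estimate for anxiety or stigma is the planned one. The trial is open-label and staff take part in outcome assessment (Blinding section), so it helps to have that settled before any comparison is seen.

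**Working it through.** **1. The text side by side**

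| Scale | Role | Baseline collected | Baseline adjustment stated in Table 2 |
|---|---|---|---|
| BDI-II (depression) | clinical primary | yes | yes |
| SHAI (anxiety) | clinical primary | yes | no |
| IARSS-6 (stigma) | clinical primary | yes | no; dichotomised |
| AFQ-Y8 (psychological flexibility) | process | yes | yes |

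(The measures column of Table 2 names other depression and anxiety scales. I follow its outcomes column and the Study instruments section.)

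One row sets four tests against three outcomes. The other sets the same four tests against a single score, the AFQ-Y8, for which no categorical version is described. No one-to-one matching of tests to outcomes is possible in either row.

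**2. The plan's own sample size**

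Inputs from the Sample size section: the difference between the ACT "arm and control arm was 4.09 while the standard deviation in the control arm was 5.13" (post-treatment RADS-2 depression scores), Z values 1.96 and 0.84, "a design effect of 2.0", and 10% loss. The Randomization section has "individuals allocated in a ratio of 1:1".

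- N = 2 × (1.96 + 0.84)² × 5.13² / 4.09² = 24.67, so 25 per arm. The protocol prints 25.1 and uses 26.
- 26 × 2 = 52; 52 / 0.90 = 57.8, so 58 per arm and 116 in total, as stated.

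The difference of one per arm does not affect this point. The calculation compares post-treatment means and takes no account of baseline.

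**3. What baseline adjustment removes**

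Residual variance after adjustment = SD² × (1 − r²), where r is the correlation between baseline and post-intervention scores. The protocol gives no r, so 0.3 to 0.7 is assumed.

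| r | Variance remaining (1 − r²) | Variance removed (r²) | Ratio of standard errors, √(1 − r²) |
|---|---|---|---|
| 0.3 | 0.91 | 9% | 0.954 |
| 0.5 | 0.75 | 25% | 0.866 |
| 0.7 | 0.51 | 49% | 0.714 |

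These ratios need no effect size or SD, so they apply to any of the scale scores, including SHAI and the 0-6 IARSS-6 total.

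**4. Power, for illustration only**

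The only effect size in the protocol is the depression one: d = 4.09 / 5.13 = 0.797. Two-sample t-test, two-sided 5%, with d / √(1 − r²) for the adjusted analysis:

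| Effective number per arm | Unadjusted | r = 0.3 | r = 0.5 | r = 0.7 |
|---|---|---|---|---|
| 26 (design effect 2.0 accepted) | 80.5% | 84.0% | 90.2% | 97.7% |
| 52 (no design effect) | 98.1% | 98.8% | 99.6% | about 100% |

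The gain is about 3 to 17 points in the first row and about 1 to 2 points in the second.

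**The case against.** Four counter-arguments deserve a fair hearing.

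- **The list may be shorthand.** The Statistical analysis section links the same tests to continuous and categorical variables, and Table 2 contains both kinds, since the IARSS-6 is dichotomised. On that reading chi-square and Fisher's exact belong to the split stigma score, and the reference to mean differences is loose wording. This largely stands for the clinical row. A reader might infer several competing primary analyses, with the result deciding which is reported. The protocol labels no test primary, and a regression on arm alone is the same test as the equal-variance t-test, so that inference goes too far. The reading does not explain why the full list is repeated for the AFQ-Y8, or whether the t-test or an adjusted regression governs.
- **Power.** A reader might infer that the trial gives up some ten points of power. The documents do not support that. The figure comes from the depression effect, and depression is an outcome that Table 2 already describes as baseline-adjusted. It also depends on the design effect of 2.0, although individuals are randomised; without it the gain nearly vanishes.
- **Validity.** A reader might take the missing adjustment as a source of bias. It is not: randomisation keeps the unadjusted comparison unbiased. A chance baseline imbalance adds noise, not systematic error.
- **Detail for the analysis plan.** The choice of covariates often belongs there, and the ANCOVA abbreviation and the ANOVA in the abstract are editorial points. That is fair. But the mismatch of test to quantity and the uneven adjustment are things the protocol states, not things it leaves out.

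**Conclusion.** The point holds as a fault of consistency and efficiency. Two statements in Table 2 need correction: tests that cannot yield the named quantity, and baseline adjustment stated for BDI-II and AFQ-Y8 but not for SHAI and IARSS-6.

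For anxiety and stigma, the precision forgone by an unadjusted analysis is 9%, 25% or 49% of the outcome variance at an assumed correlation of 0.3, 0.5 or 0.7. In terms of confidence-interval width that is roughly 5%, 13% or 29% (1 − 0.954, 1 − 0.866, 1 − 0.714). If the correlation is near zero, adjustment gains nothing and costs one degree of freedom.

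No loss of power is shown for these two outcomes, because the protocol gives neither an effect size nor an SD for them. The change is worth making because the data and the method are already in the plan.

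**What to change.** In both rows of Table 2, replace the list of tests with one between-arm analysis for each scale score: a linear regression (ANCOVA) of the post-intervention score on arm and the baseline score of the same scale, reporting the adjusted mean difference with its 95% CI. Site may be added as a covariate. Apply this to SHAI and to the IARSS-6 total as well as to BDI-II and AFQ-Y8. State that chi-square and Fisher's exact tests are for categorical outcomes only, such as the dichotomised IARSS-6. Bring the abstract into line.

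The cost is wording only. Linear regression is already listed, the baseline scores are already collected, and SPSS, the named package, fits the model.
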